### Sample size

To calculate the sample size, we determine the minimum detectable effect size based on the best available data in the literature regarding the effects of educational programs on adoption of insect farming. In Ghana, Kenya and Uganda, insect farming remains relatively uncommon compared to other types of farming activities. For instance, in a pilot study on cricket (*Scapsipedus icipe*, *Acheta domesticus)* farming in Kenya, only 12% of the sampled farmers adopted cricket farming [28]. We use this information to determine the minimum detectable effect size in our power analysis. We assume a minimum detectable effect size of 0.25 for Kenya, as an effect size of 0.12 would be too small to be detected given the available budget for the study. In Ghana, 560 farmers were trained as part of a pilot project focusing on farming Palm Weevil (*Rhynchophorus phoenicis*) production near their homes or gardens [34]. The same study reported that 48% of the trained farmers were actively farming Palm Weevil after the training. To avoid overestimation of the effect size, we consider a minimum detectable effect size of 0.25 for Ghana. In Uganda, pilot studies indicating the proportion of farmers involved in the farming of African bush crickets (*Ruspolia differens Serville*) were not found. Thus, we refer to related studies on the adoption of climate-smart agriculture practices in Uganda. Accordingly, we assume a minimum detectable effect size of 0.25 based on a previous study concerning climate-smart agricultural interventions [35].

Using the Optimal Design Software for multilevel and longitudinal research [36], the sample size is calculated based on a 0.8 power, 0.05 significance level and 0.06 intra-cluster correlation coefficient. Fig 2 shows that a total of 64 clusters (villages), each with 15 participants, are needed to obtain 80% of power for cluster randomized designs with two intervention groups. The minimum sample size across each of the intervention and control arms thus includes 32 villages in each country. To ensure that we detect the same effect size or smaller, we increase the sample size to 33 villages for each of the intervention and control arms.

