**Fig 2 pone.0288870.g002:**
[figure not shown]
Power versus number of clusters.

Based on our experience from previous farming and nutrition intervention studies in the three countries, we expect an attrition rate of no more than 10%. Thus, the number of participants is increased by 10% to accommodate for attrition in our sample size calculation. To reduce the attrition rate, the implementation team visits the participants frequently to address any concerns related to the intervention. The implementation team also arrange alternative meeting schedules in case the participant is unavailable during endline surveys. Any missing values resulting from attrition are dropped from data analysis.

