Study arm	Clusters	Baseline survey	Intervention with participant endline survey			Community endline survey
	Villages	Participants^a^ per village	Participants per village	Participants per arm	Participants per arm (extra 10% added)^b^	Participants per village^c^
Treatment *P*	33	30	15	495	545	15
Treatment *PC*	33	30	15	495	545	15
Control	33	30	0	0	0	30

Note: ^a^ Participants are household represented by the head of the household.

^b^ The number of participants per treatment arm was increased by 10% to account for attrition.

^c^ The remaining 15 participants per village from the baseline survey who are not part of the intervention are included in the community endline survey. No interventions are implemented in the control villages, therefore, all the 30 household are included in this survey.

To ensure research integrity and methodological rigor, the village randomization process is blinded to all individuals involved in the research and households residing in the 99 villages prior to the intervention. A randomized sequence is generated in STATA [41] by a colleague not involved in the research. The outcome of the randomization is only revealed to project staff and households after the randomization process is completed. During the intervention, blinding is not maintained, except in the control villages where households are unaware of the intervention. Project staff members only visit control villages during the baseline and endline surveys, and no visits are conducted during the intervention to prevent information leakage and reduce potential biases that could arise from knowledge of the intervention in the control group.

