### Outcomes

#### Overview of outcome variables and measurements

*Primary outcomes variables*. The primary outcome variables indicating the impacts of the interventions are: 1) whether farmed insects are consumed in the household, and 2) adoption of insect farming. The first primary outcome variable is measured during the baseline and endline surveys using questionnaires that inquire whether the participants cook and consume farmed insects. For participants, who cook and consume the farmed insects, they are asked to indicate the frequency of consumption within the last one year using a five-point scale ranging from 1–3 times per month to 1 or more times per day. The second outcome variable is measured through direct observation to determine whether the participant is still engaged in insect farming at the time the endline survey is conducted. Engaging in insect farming activities entails management of an insect farm, as well as harvesting and postharvest practices, as described in Table 2.

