### Analysis plan

We focus on the intent-to-treat (ITT) effects. Some participants may not attend to the agricultural training or nutrition education sessions despite being invited to the sessions. In the ITT analysis, we estimate the effects of the interventions by including all participants irrespective of whether they participated in the interventions or not. Our basic regression framework to estimate the ITT effect is:

$$Y_{i}=\beta_{0}+\beta_{1}T_{1}+\beta_{2}T_{2}+\varepsilon_{i}$$
(1)

*Y_i_* is the outcome variable for individual *i*, *T*_1_ and *T*_2_ are dummy variables which take the value 1 depending on which intervention the household in a village was assigned, 0 otherwise. The random error term is represented by *ε_i_*. The impacts of the interventions are given by *β*_1_ and *β*_2_. Standard errors are clustered at the village level to account for within village correlations. We conduct further analyses by extending Eq (1) to account for vectors of individual characteristics and other control variables, baseline and endline data, and treatment heterogeneity in terms of differences in the effects of the two interventions–*Treatment P* and *Treatment PC*. We assess any spillover effects by interviewing households who did not participate in the intervention. This assists in understanding whether and how the information regarding insect farming and consumption spread beyond the targeted households in the intervention [37].

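### Dropping missing endline values is the only stated handling of attrition; it does not fit an ITT analysis of all participants and can bias the adoption effects

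*Protocol article*

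**What the plan says.** All references are to the protocol article.

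- **Sample size** (text after Fig 2). The investigators write that "we expect an attrition rate of no more than 10" percent, enlarge the sample accordingly, and describe frequent visits and rescheduled endline meetings to limit loss. The paragraph ends with the analysis rule: "Any missing values resulting from attrition are dropped from data analysis". The note to Table 1 repeats the enlargement: "The number of participants per treatment arm was increased by 10% to account for attrition".
- **Analysis plan.** "We focus on the intent-to-treat (ITT) effects". The explanation that follows is that "we estimate the effects of the interventions by including all participants irrespective of whether they participated in the interventions or not".
- **Outcomes.** Adoption, one of two primary outcomes, is "measured through direct observation to determine whether the participant is still engaged in insect farming at the time the endline survey is conducted". The other, consumption of farmed insects, comes from the questionnaire.
- **Contact by arm.** Under Components of Treatment P, the implementation team visits each participating household monthly or more often. Table 5 adds output monitoring in the treatment groups only. Under Recruitment and randomization, control villages see project staff only for the two surveys.

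The article sets no missing-data assumption and no sensitivity analysis beside the deletion rule.

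**The concern.** This is a rule the article states, not a detail left for a later document. Followed as written, it makes the primary analysis complete-case, so the analysed set is the households found at endline rather than all those the ITT statement covers.

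Two features of the design make it plausible that the households found are not a random subset. First, the main retention measure is contact by the implementation team, and that contact exists only in the treatment arms. Second, the outcome is continued farming, so disengaging from the project could both produce a negative outcome and make a household harder to reach. If loss depends on arm and outcome, deletion biases each treatment-versus-control effect. It can also bias the P versus PC contrast, which isolates the nutrition education component. The 10% sample enlargement protects power and does nothing about bias.

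**Working it through.** **1. The plan's own sample size.** Inputs from Sample size: "the sample size is calculated based on a 0.8 power, 0.05 significance level and 0.06 intra-cluster correlation coefficient", effect size 0.25, 15 participants per village. I assume a two-sided test and read 0.25 as a standardised difference.

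- Noncentrality λ = δ / √[4(ρ + (1−ρ)/n)/J], with δ = 0.25, ρ = 0.06, n = 15, referred to a noncentral t with J − 2 df.
- J = 64 gives power 0.803 and J = 62 gives 0.790. The stated 64 villages are reproduced.
- Cross-check: 252 per arm × design effect (1 + 14 × 0.06 = 1.84) = 464, and 464/15 ≈ 30.9 villages per arm by the normal approximation.
- With 66 villages and 10% loss (15 × 0.9 = 13.5 analysed per village), power is 0.793. The power cost is minor, so the issue is bias.

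**2. Complete-case adoption at loss a = 0.10.** The true rates p are the 12% Kenyan pilot figure, an illustrative 25%, and the 48% Ghanaian pilot figure.

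| Who is lost | Formula | p = 12% | p = 25% | p = 48% |
|---|---|---|---|---|
| All non-adopters | p/(1−a) | 13.3% | 27.8% | 53.3% |
| Adopt at half the observed rate | p/(1−a/2) | 12.6% | 26.3% | 50.5% |
| Adopt at the same rate | p | 12% | 25% | 48% |
| All adopters | (p−a)/(1−a) | 2.2% | 16.7% | 42.2% |

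The largest upward bias is 1.3, 2.8 or 5.3 points. The sign depends entirely on who is lost.

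**3. Effect against control.** Eligible villages have had no insect farming exposure, so control adoption near zero is a reasonable assumption. Control losses then barely move the control rate, and the treatment-arm bias passes into the effect. If control adoption were 5% and treated adoption 25% (true difference 20 points), with only non-adopters lost:

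- 10% loss in both arms: 0.25/0.9 − 0.05/0.9 = 22.2 points.
- 10% treated and 5% control: 0.25/0.9 − 0.05/0.95 = 22.5 points.

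**4. P versus PC.** Assume 15% loss in P and 5% in PC (mean 10%), only non-adopters lost, no true difference. The spurious difference is p/0.85 − p/0.95:

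- p = 25%: 29.4% − 26.3% = 3.1 points.
- p = 48%: 56.5% − 50.5% = 5.9 points.

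A 0.25 SD difference on the proportion scale is 0.25√[p(1−p)]:

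- p = 25%: 0.25 × 0.433 = 10.8 points, and 3.1/10.8 ≈ 29%.
- p = 48%: 0.25 × 0.500 = 12.5 points, and 5.9/12.5 ≈ 47%.

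**5. Bounds.** With 10% missing and an observed rate q, the full-sample rate lies between 0.9q and 0.9q + 0.1. For q = 25% that is 22.5% to 32.5%, always 10 points wide per arm.

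**The case against.** The strongest defence is that the ITT sentence is about attendance. Households that skip sessions but are surveyed stay in, and the sentence does not speak to unobserved endline outcomes. That stands: a reader might infer a flat contradiction, but what the article supports is an unreconciled inconsistency. A household that was invited, disengaged and could not be found at endline is covered by the ITT statement and removed by the deletion rule.

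Second, nothing in the article says that households which stopped farming are the likeliest to be missing, or that loss occurs only after kits and training. Control households also face a year between surveys. The eligibility rule on permanent residence, the regular visits and the rescheduled meetings all work to limit loss. So a reader might infer that adoption will be overstated, but that is an assumption; the bias could be zero or downward.

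Third, the 15% versus 5% split is hypothetical, and 15% in one arm exceeds the expected maximum. Against a control arm with no adopters, loss confined to non-adopters only rescales the effect by 1/0.9 at 10% loss; it cannot create one. This also stands, but it does not cover P versus PC, where unequal loss can create a difference from nothing.

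Fourth, the rule drops missing values. One might infer that adoption seen at a homestead would be discarded when the head is away; the wording does not say so. Nor is such observation always possible: farming is typically indoors, so access and consent are needed.

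Finally, sensitivity analyses often belong in an analysis plan. Their absence from an article would be no finding. The point here is the rule that the article does state.

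**Conclusion.** The concern holds in limited form. Complete-case deletion, as the only stated handling of attrition, is inconsistent with an ITT analysis of all participants and can bias the primary effects. At 10% loss the largest upward bias in an arm's adoption rate is a factor of 1/0.9, that is 1.3 points at 12%, 2.8 at 25% and 5.3 at 48%. This rests on all lost households being non-adopters; carrying it over to the effect against control also needs control adoption near zero. For P versus PC, the assumed 15%/5% split gives a spurious 3.1 to 5.9 points, about 30–50% of a 0.25 SD difference. It would be tempting to call that as large as the effect the trial can detect; the figures do not support this. The direction remains unknown until attrition is seen, which is the reason to show a range instead of one complete-case number.

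**What to change.** Replace the deletion sentence in Sample size, and align the Analysis plan with it, so that the complete-case result is reported together with:

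- (a) attrition compared across all three arms;
- (b) for adoption, an analysis counting lost households as not farming, plus Lee or worst-case bounds;
- (c) for survey outcomes, including consumption of farmed insects, inverse-probability-of-response weighting built from the baseline survey.

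Where access and consent allow, field staff should record observed adoption even if the household head cannot be interviewed, and those values should stay in the analysis.

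The analytical cost is a few extra analyses on data already held, and wider reported uncertainty. The field step needs an instruction to survey teams and a check that consent covers it. Trial status says follow-up data collection had not begun at submission, so on the article's own timing the change can be made before endline.

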### Recruitment and randomization

A multilevel sampling procedure is used to identify and select the villages and participants included in the study (Fig 3). In terms of regions and districts, study sites are selected considering infrastructure accessibility and availability of rural areas with a large number of villages. In addition, areas with traditional insect consumption are selected to facilitate the adoption of insect farming. Previous studies on the adoption of new agricultural technologies and new food varieties suggested that previous consumption is an essential driver of adoption [25, 28, 37, 38]. Once the study sites are identified in each country, eligible villages are selected based on a range of inclusion and exclusion criteria. A village is eligible for the intervention if:

It has not been exposed to previous insect farming activities, including formal insect farming trainingIt has at least 60 householdsIt is not located adjacent to another village previously exposed to insect farmingThere are no active agricultural intervention in the village

**Fig 3 pone.0288870.g003:**
[figure not shown]
Flow diagram for the study.

In addition, selected villages should not share common boundaries to reduce the risk of unintended spillover effects between treatment and control groups. Based on the above criteria, a list of 200 eligible villages is generated in Excel per country. Using Excel’s function to generate random numbers, 99 villages are randomly selected for the study in each country.

Households are selected and recruited based on a random walk door-to-door recruitment procedure as it is impossible to find a pre-existing list of households. Depending on the number of households in a village, every second or third household is approached for recruitment until a total number of 30 households in a village have been recruited to participate in a baseline survey. To be eligible, residents of the household must:

Have children below five years of age, as nutrition interventions usually target these groups of the population in Africa;Live permanently at the same address;Be able to participate in the agricultural training and nutrition education sessions;Be able to perform insect farming and be able to provide the required space and housing for insect farming; andSeek information to solve problems with his/her own agricultural production

The fourth criterion is needed because household insect farming is typically carried out indoors, either in a separate room or in a separate building close to the main house, to prevent theft of materials and protect against predators [21, 26]. Additionally, the availability of suitable space was identified to be one of the barriers to insect farming [28]. We assess farmers’ ability to provide space by observing the type of construction material used in their houses, specifically by determining whether the material consists of corrugated metal roofs and semi-permanent building materials. The fifth criterion is needed to acknowledge the fact that access to information plays a crucial role in driving the adoption of new agricultural technology by enabling farmers to understand potential risks and challenges, and take necessary precautions to minimize risk [39, 40]. Since insect farming represents a new farming system that may be perceived as a risky venture by farmers [28], which, in turn, could deter adoption, we include only households that actively seek information to solve problems with their own agricultural production. We measure farmers’ information-seeking behavior by asking them whether they seek information from sources such as agricultural extension offices, community groups (such as women’s groups and farmer group), churches/mosques, mass media, and the internet, when they face problems.

Once households are determined to be eligible, household heads are approached, and informed consent is sought. After obtaining consent, they are invited to participate in the baseline survey. Once the baseline surveys are completed and the relevant information is gathered, the 99 villages are randomly assigned to the intervention and control groups (see Fig 3) using computer-generated random numbers. Out of the 30 household heads participating in the baseline survey in each village in the two intervention arms, a simple random draw lottery is used to select 15 household heads to participate in the intervention. The remaining 15 household heads that are not selected for intervention still participate in the community endline survey (see Table 1). The purpose of this survey is to assess whether and how the information regarding insect farming and consumption has spread beyond the households included in the intervention [37].

**Table 1 pone.0288870.t001:** Number of clusters and participants per country.

Study arm	Clusters	Baseline survey	Intervention with participant endline survey			Community endline survey
	Villages	Participants^a^ per village	Participants per village	Participants per arm	Participants per arm (extra 10% added)^b^	Participants per village^c^
Treatment *P*	33	30	15	495	545	15
Treatment *PC*	33	30	15	495	545	15
Control	33	30	0	0	0	30

Note: ^a^ Participants are household represented by the head of the household.

^b^ The number of participants per treatment arm was increased by 10% to account for attrition.

^c^ The remaining 15 participants per village from the baseline survey who are not part of the intervention are included in the community endline survey. No interventions are implemented in the control villages, therefore, all the 30 household are included in this survey.

To ensure research integrity and methodological rigor, the village randomization process is blinded to all individuals involved in the research and households residing in the 99 villages prior to the intervention. A randomized sequence is generated in STATA [41] by a colleague not involved in the research. The outcome of the randomization is only revealed to project staff and households after the randomization process is completed. During the intervention, blinding is not maintained, except in the control villages where households are unaware of the intervention. Project staff members only visit control villages during the baseline and endline surveys, and no visits are conducted during the intervention to prevent information leakage and reduce potential biases that could arise from knowledge of the intervention in the control group.

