#### Components of *Treatment P*

*Agricultural training on insect farming*. The agricultural training has been designed to teach intervention participants about small-scale insect farming. A training manual has been developed to ensure that the same information is transmitted to all participants. The training is based on behavior change techniques and key messages in relation to successful insect farming [42]. It covers a range of topics relevant to promoting insect farming for consumption. The topics are divided into six main elements, as shown in Table 2. Extensive training is provided in all villages where the *Treatment P* is implemented. The 15 participating household heads per village are divided into two groups during training sessions to ensure effective information dissemination to each participant and smooth feedback discussions. The training is conducted within one day and is organized into several sessions, scheduled to follow the main elements outlined in Table 2.

**Table 2 pone.0288870.t002:** Main elements of the agricultural training intervention.

Overall topic	Specific information
**1. Introduction**	• Welcome • Elements of the training sessions • Time schedule
**2. Overview of insects as nutritious and healthy food**	• Insects as food for human consumption • Benefits of insect farming
**3. Ecology and Biology of insects**	• Insect life cycle • Sex determination in insects • Insect behavior
**4. Starting an insect farm**	• Rearing house and site selection • Rearing equipment • Rearing container • Cage arrangement
**5. Management of an insect farm**	• Insect feeding and watering • Knowing signs and timing of egg laying • Preparing egg-laying substrate • Egg collection, incubation and hatching • Caring for pinhead • Hygiene maintenance • Pest and disease control
**6. Harvesting and post-harvest handling**	• Harvesting methods • Storage and transportation of insects • Post-harvest insect processing methods

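### Table 1's 545 participants per treatment arm, the 10% attrition allowance, cannot come from a scheme that draws exactly 15 of 30 households in each of 33 villages (495)

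*Protocol article*

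**What the plan says.** Under Sample size, the article states that "a total of 64 clusters (villages), each with 15 participants, are needed to obtain 80% of power" and then that "we increase the sample size to 33 villages for each of the intervention and control arms". It expects attrition of at most 10%, says that "the number of participants is increased by 10% to accommodate for attrition in our sample size calculation", and drops values lost to attrition from the analysis. Table 1 carries this through: each treatment arm has 15 participants per village, 495 per arm, and 545 in a further column that adds 10%. Note b repeats that "The number of participants per treatment arm was increased by 10% to account for attrition".

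The operational text gives a different count. Under Recruitment and randomization, recruitment stops at 30 households per village. In the intervention villages "a simple random draw lottery is used to select 15 household heads to participate in the intervention", and the 15 not drawn go to the community endline survey (also Table 1, note c). Under Components of Treatment P, "The 15 participating household heads per village are divided into two groups during training sessions". Under Data collection, the participant endline survey is held with the 15 who take part, and the community survey with the remaining 15. In control villages all 30 are surveyed at endline.

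**The concern.** The article gives two sizes for the same treatment arm, 495 and 545, and only one of them fits the way households are recruited and drawn. Losses are dropped from the analysis and no replacement is described, so over-enrolment is the only numerical allowance for attrition that the article claims within the treatment arms. If the extra households were never drawn, that allowance is absent.

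Two things depend on the answer. One is the denominator for the intention-to-treat analysis and for the attrition rate, which is 495 or 545 per arm. The other is the account of why the trial keeps its power when households are lost. A reader of Table 1 would expect about 490 analysed per treatment arm after a 10% loss, whereas the sampling scheme leaves about 446.

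**Working it through.** **Inputs.** From Sample size: "the sample size is calculated based on a 0.8 power, 0.05 significance level and 0.06 intra-cluster correlation coefficient"; an effect size of 0.25 ("We assume a minimum detectable effect size of 0.25 for Kenya", and the same value for Ghana and Uganda); 32 villages per arm required and 33 planned; attrition of at most 10%. From Recruitment and randomization and Table 1: 30 households recruited per village, 15 drawn in treatment villages, 30 followed in control villages.

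**Step 1: reproduce 545.** 33 × 15 = 495, and 495 × 1.10 = 544.5, which rounds up to 545. The figure follows the article's own rule.

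**Step 2: can the scheme supply it?** 545 / 33 = 16.5 per village. The article gives 15 drawn plus 15 for the community survey, which uses all 30 recruited. Drawing 16 or 17 would leave 14 or 13 for the community survey, not 15. No section mentions 16 or 17 drawn, or 13 or 14 remaining. The shortfall is 545 − 495 = 50 per arm.

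**Step 3: numbers analysed at 10% loss.**
- 495 × 0.9 = 445.5 per treatment arm (13.5 per village).
- 545 × 0.9 = 490.5, had 545 been enrolled.
- The calculated requirement is 32 × 15 = 480.

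**Step 4: power.** For a two-level cluster-randomized comparison with J villages per arm, m₁ and m₂ households analysed per village, effect d and ICC ρ:

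λ = d² / { [ρ + (1 − ρ)/m₁]/J + [ρ + (1 − ρ)/m₂]/J }

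Power comes from the non-central F distribution with 1 and 2J − 2 degrees of freedom, with d = 0.25, ρ = 0.06 and two-sided α = 0.05.

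The plan's own figure first, J = 32 and m = 15: ρ + (1 − ρ)/15 = 0.06 + 0.0627 = 0.1227; 2 × 0.1227/32 = 0.00767; λ = 0.0625/0.00767 = 8.15; power 80.25%. This reproduces the stated 80% with 64 villages.

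| Comparison, 33 villages per arm | Analysed per village | λ | Power |
|---|---|---|---|
| Equal sizes, no loss | 15 and 15 | 8.41 | 81.5% |
| P vs PC, 5% loss | 14.25 and 14.25 | 8.19 | 80.5% |
| P vs PC, 10% loss | 13.5 and 13.5 | 7.96 | 79.3% |
| Treatment vs control, 10% loss | 13.5 and 27 | 9.19 | 84.7% |
| Equal sizes, 545 enrolled, 10% loss | 14.86 and 14.86 | 8.37 | 81.3% |

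For P vs PC, 14 per village (6.7% loss) gives 80.1%, so power passes below 80% at a loss of roughly 7%.

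**The case against.** The strongest reply is that little depends on the missing allowance. The Analysis plan takes the two coefficients against control as the impacts of the interventions and places the difference between P and PC among further analyses. The contrasts with control keep about 85% power at the maximum loss. Ten percent is an upper bound, not a forecast, and the article also plans frequent visits and rescheduled endline meetings to limit loss. All of this stands, and it limits the consequence. It does not reconcile 545 with 15 per village.

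A reader might infer two stronger points, and the article supports neither.

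- *That power falls below 80%.* This holds only for P vs PC, only when loss exceeds roughly 7%, and then by 0.7 percentage points at the 10% bound.
- *That 545 is an arithmetic error because 495 / 0.9 = 550.* Dividing by the expected retention is the better convention, but the article says it adds 10%, and 545 does that. The two differ by five participants (0.9%). The 490.5 left from 545 would still exceed the calculated requirement of 480.

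A further caution is that the article never says 0.25 is in standard-deviation units, and it discusses the value beside adoption proportions of 12% and 48%. The power figures depend on the standardized reading. The count contradiction does not.

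**Conclusion.** The contradiction holds. The article claims a 10% over-enrolment to 545 per treatment arm that its sampling scheme does not contain: 495 can be drawn, and the other 50 have no source. At the stated maximum loss about 446 per treatment arm remain.

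The statistical consequence is small: about 85% power for each treatment against control and about 79% for P against PC. What protects the trial is the 33rd village per arm and the 30 households followed per control village, not an inflated treatment arm. These figures are per country. They assume that 0.25 is a standardized effect (the reading that reproduces the stated 64 villages), that the test is two-sided, and that loss is spread evenly over villages and arms.

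**What to change.** State the number of households actually drawn per treatment village. Trial status says recruitment is complete and the intervention is under way, so the number is known.

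- **If 15 were drawn:** delete the 545 column, note b and the Sample size sentence on the 10% increase. State 495 enrolled and at least about 446 analysed per treatment arm at 10% loss. Give power at that loss as about 85% for each treatment against control and about 79% for P against PC, with the standardized-effect assumption written out, and say that the margin comes from the extra village and the larger control clusters.
- **If 16 or 17 were drawn:** correct the counts of 15 under Recruitment and randomization, in Table 1 and its note c, under Components of Treatment P and under Data collection, including the number left for the community survey.

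The cost is wording and a table correction, plus a slightly less favourable power figure for P against PC in the first case. It should be on record before endline attrition is reported. No recruitment or redesign is needed.
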